## 225 **Quality control**

226 The quality control team was established prior to this study. All the researchers  
227 involved in this study must attend the complete operation training, including study  
228 protocol and standard operating procedures of participants' data collection. In addition,  
229 both on-site and on-line review for data verification will be implemented, to ensure  
230 the quality and consistency of organizational operations, and stabilize food supply at  
231 the canteen.

232

## 233 **Statistical analysis**

234 The Mann-Kendall test will be implemented to examine the temporal trends of  
235 lunchtime food supply based on average “traffic light” score and animal/plant food  
236 ratio. For dietary record, we hypothesized that at least 5000 person-meal observations  
237 would be collected and analyzed over the follow-up period. Generalized linear mixed

models with intervention, time and 2-way interaction as fixed factors, will be used to examine the intervention effects on each outcome. A two-sided  $p$  value  $< 0.05$  will be considered to indicate statistical significance.

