## Methods

### Setting and study design

This trial is a two-arm parallel, randomized, controlled study in real-world situations. This smartphone applet with built-in AI-based algorithm only takes effect where dishes prepared by recipes with quantity (in China, same dish prepared at different home are different in cooking but dishes in central kitchen or food factory are prepared strictly following standard cooking procedure ). Participants are enrolled sequentially until the sample size reaches requirement. This study will be carried out in a pilot company employing 3000 people and food is prepared by the central kitchen at staff canteen. All participants will choose and consume meals on their own wills during the study. Weight and blood pressure measuring tools placed at the canteen can be available to participants; therefore, they can conveniently measure and record anthropometric indicators through the applet.

**Phase I.** The employees will be recruited to dine in the canteen for 3 months, assigned to the intervention or control group randomly. Both groups will be asked to use the applet to record their lunch each weekday during the study. After 1 week of run-in period, the intervention group will be able to access the information of dish nutrition evaluation and PN evaluation after meal consumption, while the control group will not. Both groups will be followed up by researchers on the same time schedules for the outcome measurements.

**Phase II.** Full-functioned applet will be available for use by all the diners (about 800) for another 1 year. Who use the applet at least 2 days per week will be regarded as the intervention group while the others will be the control group. During this phase, metabolic indicators from the annual physical examination will be provided by the company.

Figure 1 outlines the study design and Table 1 presents the visits and data

60 collection schedule.

61

62 Figure 1. Study design of the trial.

[figure not shown]

63

64

65 Table 1. Visits and data collection schedule

|                           | Phase I (3 months) |        |           | Phase II (1 year) |        |           |
|---------------------------|--------------------|--------|-----------|-------------------|--------|-----------|
|                           | Screening          | Run-in | Follow-up | Screening         | Run-in | Follow-up |

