## 67 Sample size

68 In Phase I, the planned sample size per group was determined as 70 to detect an  
 69 assumed intervention effect size of 0.25 in animal/plant food ratio over 4 months.  
 70 Statistical power was set at 90% with a significance level of 5%, using an SD in  
 71 animal/plant food ratio of 0.41 from the Shanghai Diet and Health Survey ,  
 72 considering a 15% dropout rate. In Phase II, assuming that the prevalence of

metabolic syndrome after intervention is approximately 20% based on the available research evidence, we would need 200 participants in each group to have sufficient power to detect the given effect size.

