### ***Randomization and blinding***

Following baseline measurements, the newly-enrolled participants will be randomized at a ratio of 1:1 to an intervention or control group. Randomization is stratified by sex and age. The trial is conducted as a double-blind study. The researchers are not blinded to allocation due to the nature of the intervention strategy, however the field investigators and participants will be blinded throughout the study, ensuring allocation concealment.

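### The listed Phase I mixed model uses neither the run-in value as a covariate nor the stratification factors sex and age; adding these already-collected variables would improve precision at no cost

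*Protocol*

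**What the plan says.** The Statistical analysis section of the protocol names one model for all outcomes: generalized linear mixed "models with intervention, time and 2-way interaction as fixed factors, will be used to examine the intervention effects on each outcome". It does not define time, does not say whether the run-in is one of its levels, and does not say which coefficient is the treatment effect.

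Two design features bear on that model:

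- Randomization and blinding: "Randomization is stratified by sex and age".
- Setting and study design, Phase I: both groups record weekday lunches, and "After 1 week of run-in period, the intervention group will be able to access" the nutrition evaluations. Table 1 schedules dietary records and anthropometric indicators at run-in and at follow-up. Each participant should therefore have a pre-access value of the dietary and anthropometric outcomes.

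**The concern.** The protocol gives an explicit list of fixed factors, and that list leaves out information the design was built to supply. Both readings of time have a drawback.

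- **Run-in is a level of time.** The treatment effect is then the interaction, a difference between arms in change from the run-in. The run-in has at most five weekday lunches, and all their noise is subtracted into the contrast.
- **Time covers follow-up only.** The run-in then plays no part. A comparison of arms is adjusted neither for baseline nor for the stratification factors. If time is also entered as a linear trend and the interaction is read as the effect, an immediate and sustained shift would produce an interaction near zero.

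What is at stake is precision, and clarity about which term is tested. Validity is not at stake.

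**Working it through.** **Inputs from the protocol (Sample size).** 70 per group: "the planned sample size per group was determined as 70 to detect an" "assumed intervention effect size of 0.25 in animal/plant food ratio over 4 months". Power and alpha: "Statistical power was set at 90% with a significance level of 5%, using an SD in" "animal/plant food ratio of 0.41 from the Shanghai Diet and Health Survey". Dropout: "considering a 15% dropout rate". The 0.25 is read as an absolute difference. The Statistical analysis section makes the test two-sided and expects at least 5000 person-meals.

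**Assumption.** The protocol gives no correlation rho between baseline and follow-up, so a range is shown.

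**1. The plan's own figure.** n = 2(1.96 + 1.2816)² × 0.41² / 0.25² = 56.5, so 57 per group; 57/0.85 gives 68. The t-test version gives 58, and 58/0.85 gives 69. The stated 70 therefore reproduces, to within rounding, as a plain comparison of two means without baseline adjustment. With 70 × 0.85 = 59.5, taken as 59 completers per group, power is 91.2%.

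**2. Change contrast against baseline adjustment.** Take one value before and one after, with equal SDs, in a linear model:

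- SD of change = 0.41 × √(2(1 − rho))
- baseline-adjusted SD = 0.41 × √(1 − rho²)
- variance ratio = 2(1 − rho)/(1 − rho²) = 2/(1 + rho)

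| rho (assumed) | Variance ratio, change / adjusted | Power, change | Power, adjusted |
|---|---|---|---|
| 0 | 2.00 | 64.9% | 91.2% |
| 0.2 | 1.67 | 74.5% | 92.2% |
| 0.3 | 1.54 | 79.9% | 93.5% |
| 0.4 | 1.43 | 85.6% | 95.1% |
| 0.5 | 1.33 | 91.2% | 96.9% |
| 0.6 | 1.25 | 95.9% | 98.5% |
| 0.7 | 1.18 | 99.0% | 99.6% |

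The ratio exceeds 1 for every rho below 1. On this approximation the change contrast is under 90% only when rho is below about 0.5.

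**3. Follow-up only, baseline unused.** The unadjusted variance is 1/(1 − rho²) times the adjusted one: 1/0.91 = 1.10 at rho 0.3, 1/0.75 = 1.33 at 0.5 and 1/0.51 = 1.96 at 0.7. Power on the planning assumptions is still the 91.2% of step 1. If sex and age explained 5%, 10% or 20% of the variance (assumed), adjusting for them alone would raise it to 92.5%, 93.7% or 95.9%.

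**4. Repeated lunches.** 5000/140 is about 36 meals per randomised participant. Assume 5 run-in lunches, 36 to 60 follow-up lunches and 59 per group.

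- If 0.41 is the SD of a single meal, the change contrast has close to 100% power at every intraclass correlation tried (0.05 to 0.5).
- If 0.41 is the between-person SD and the within-person SD is w times that, the SD of change is 0.41 × w × √(1/5 + 1/k) for k follow-up lunches. At w = 2, power is 93.4% (k = 36) to 94.5% (k = 60). At w = 3 it is 63.8% to 66.0%. The baseline-adjusted contrast has 99.3% to 99.6% at w = 2 and 93.9% to 96.1% at w = 3.

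The protocol does not say which kind of SD 0.41 is and gives no within-person SD.

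**The case against.** The strongest reply is that the Statistical analysis section is a short summary. Covariates, the coding of time and the handling of baseline are commonly left to an SAP, which was not available here. Nothing in the section forbids covariates, and omitting stratification factors generally makes a test conservative, not invalid. This limits the point to an improvement. It does not remove it, because the protocol does name its fixed factors and the alternative is better on data already collected.

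Three stronger readings are tempting, and the documents do not support them.

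- **That the trial misses 90% power.** This needs the effect to be read from a contrast with the run-in, and then either a rho below about 0.5 on single values or large meal-to-meal variation. None of these is documented. A follow-up-only comparison meets the plan at 91.2%, and repeated lunches may keep even the change contrast above 90%.
- **That the effect is read from the interaction.** This is a natural reading, but the protocol says only that the model examines intervention effects. The near-zero interaction under a linear trend is likewise only a possibility.
- **That omitting sex and age makes standard errors too wide whatever the contrast.** In near-balanced data these time-constant factors largely cancel from a within-person change contrast. The loss falls mainly on a follow-up comparison of arms.

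**Conclusion.** The point holds as an improvement to a stated model. Under either reading of time, the listed factors make poorer use of the design than a baseline-adjusted model with sex and age. The change contrast has 1.54, 1.33 and 1.18 times the baseline-adjusted variance at rho 0.3, 0.5 and 0.7. A follow-up-only comparison ignores the run-in and, without sex and age, tends to be conservative.

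These ratios assume a linear model, equal SDs, one value before and one after, and no allowance for the degrees of freedom spent on covariates. The values of rho are assumptions. Whether power falls short of 90% cannot be settled from the protocol.

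**What to change.** For each Phase I outcome, state that post-run-in values are analysed with these terms:

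- fixed effects: intervention, time, intervention-by-time, the participant's run-in (baseline) value of that same outcome, sex and age;
- a participant random effect.

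Name the average post-run-in difference between arms as the treatment effect, and make the intervention-by-time term supportive. For diet, the baseline is the participant's run-in mean. For weight, BMI, body composition and blood pressure, it is the run-in measurement. If an outcome has a single follow-up value, the time terms and the random effect drop out and the model is an ordinary analysis of covariance.

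A random effect for calendar day, because diners share a menu, is optional and separate from this point.

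The cost is analysis wording only. Sex and birthdate are collected through the applet (Recruitment and follow-up), and run-in values are scheduled in Table 1. The sample size of 70 per group can stand: on its own assumptions the baseline-adjusted contrast has at least 91.2% power at any rho in the simple calculation. Trial status says the protocol was completed before any data were received; the change should be made while outcome data are still unseen.

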**Trial status**

The recruitment for the trial was initiated in September 2022, but the field work of Phase I suspended in December 2022 due to the COVID-19 epidemic. Subsequent work is under arrangement at the time of submission. This protocol was completed before the research team had received any data.

**Abbreviations**

|      |                                 |
|------|---------------------------------|
| PN   | Personalized nutrition          |
| AI   | Artificial intelligence         |
| NCDs | Non-communicable diseases       |
| RDs  | Registered dietitians           |
| DTRs | Registered dietetic technicians |
| RCTs | Randomized controlled trials    |
| CNNS | China National Nutrition Survey |
| PAL  | Physical activity level         |
| TEE  | Total energy expenditure        |
| REE  | Resting energy expenditure      |
| DRI  | Dietary Reference Intakes       |
| BMI  | Body mass index                 |

